## Abstract

**Background:**

Juvenile drug treatment courts (JDTC) have struggled to define themselves since their inception in 1995. Early courts followed a format similar to adult drug courts, but these did not address the unique needs of juveniles, which led to the creation of 16 Strategies by a consensus panel of practitioners and researchers. But, like the first JDTCs, research with courts following these strategies failed to provide convincing evidence that this “model” was associated with significant reductions in recidivism or drug use. More recently, a new set of evidence-based guidelines were developed through meta-analyses commissioned by the Office of Juvenile Justice and Delinquency Prevention (OJJDP, 2016).

**Method:**

OJJDP provided funding for a rigorous multi-site evaluation of the guidelines. This study protocol paper for the Juvenile Drug Treatment Court (JDTC) Guidelines Cross-Site Evaluation presents research designs for the comparison of youth outcomes from 10 JDTCs compared with 10 Traditional Juvenile Courts (TJCs) in the same jurisdictions. Two sites opted into a randomized controlled trial (RCT) and eight sites chose to follow a regression discontinuity design (RDD). Youth data are captured at baseline, and at 6- and 12-month follow-ups using an interview comprised of several standardized assessments. The youths’ official records also are abstracted for recidivism and substance use information. The degree to which the evidence-based guidelines are implemented at each site is assessed via an in-depth court self-assessment collected at baseline and again 2 years later and via structured site visits conducted once during implementation.

**Discussion:**

As a field-based trial, using both RCT and RDD designs, findings will provide important, policy-relevant information regarding the implementation of the OJJDP evidence-based guidelines, including the degree to which JDTCs adopted and/or modified these practices, their relative impact on recidivism and substance use, as well as the degree to which JDTCs differ from TJCs. Specific inferences may be drawn about whether following or not following specific guidelines differentially impact youth outcomes, yielding recommendations about the translation of this information from research-to-practice for potentiating the broader adoption of these guidelines by JDTCs nationwide.

**Clinical trials registration:**

This was not an NIH supported trial. The funder, OJJDP/NIJ, instead required publishing the design with even more information at https://www.ojp.gov/ncjrs/virtual-library/abstracts/juvenile-drug-treatment-court-jdtc-guidelines-cross-site-evaluation.

## Background and rationale

### Evolution of juvenile drug court standards

To address the significant increase in youth adjudicated for substance use and related offenses, juvenile drug treatment courts (JDTC) were first established in 1995, emulating the first adult drug treatment court model established in 1989, in Miami, Florida. Unlike adult drug courts that received extensive attention by researchers, practitioners, and policy makers, JDTCs flew “under-the-radar” for many years with few effectiveness studies conducted, with most of these studies showing a negligible and mixed impact on recidivism and drug use (Dennis et al., 2016; Ives et al., 2010; Wilson et al., 2019).

From their beginning, JDTC practitioners and researchers noted that the key components of the adult drug treatment court model (National Association of Drug Court Professionals (NADCP), 1997), lacked important elements needed to address the specific, unique needs of youth in the juvenile justice system (Dennis et al., 2016; Hiller et al., 2010; Stein et al., 2015). For example, absent from the 10 Key Components was a specific focus on families. Therefore, revisions were needed to indicate strategies designed to engage the family, like family therapy, to increase chances for improved outcomes for the youthful offenders.

Building on the experiences of the first decade of JDTCs, a workgroup was formed to develop youth-focused guidelines, resulting in the publication, *Juvenile Drug Courts: Strategies in Practice* (Bureau of Justice Assistance (BJA), 2003). Often referred to as the 16 Strategies, they retained key components, including an interdisciplinary non-adversarial team, involvement of a judge, and on-going evaluation and planning, and modified several others. For example, Strategy #8 called for tailoring treatment to the developmental needs of adolescents. Strategy #12 focused on recognizing and engaging the family as a valued component (often interpreted as a suggestion to use family therapy). Strategy #11 focused on the strengths of youth and their families, and Strategies #9 and #10 called for providing gender appropriate- and culturally-sensitive treatment, respectively. These strategies were adopted by the National Council of Juvenile and Family Court Judges (NCJFCJ) as the training curricula for jurisdictions planning new JDTCs.

A multi-site process evaluation by Butts and Roman (2004) showed significant variation in how JDTCs were implemented, consistent with other studies (e.g., Hiller et al., 2010; Mericle et al., 2014; Sullivan & Latessa, 2011). This finding underscored the difficulty in determining the fidelity of implementation according to the Strategies, prompting van Wormer (2010) to develop a survey designed to measure the degree to which courts were following the 16 Strategies. Concurrently, a growing effectiveness literature, summarized in several meta-analyses (e.g., Mitchell et al., 2012; Tanner-Smith et al., 2016a, 2016b; Wilson et al., 2019) continued to show an inconsistent impact of JDTCs, and JDTCs seemed to become imperiled, with one state closing all of its JDTCs. To bolster the JDTC model, a demonstration program merged the evidence-based practice, *Reclaiming Futures*, with the juvenile drug court (Dennis et al., 2016).

### Juvenile drug treatment court guidelines

By 2014, with continued concern over the mixed findings regarding the impact of JDTCs, the Office of Juvenile Justice and Delinquency Prevention (OJJDP) launched a 6-year plan to better understand the current state of research on JDTCs, develop a new set of guidelines based on this evidence, and evaluate the effectiveness of the new guidelines.

The first phase of the OJJDP effort involved conducting a meta-analysis of studies that included a comparison of JDTCs to Traditional Juvenile Courts (TJCs), as well as convening panel discussions with expert practitioners and researchers. The meta-analysis examined 41 experimental or quasi-experimental evaluations and found, on average, no differential effect on general recidivism, recidivism for drug law violations, and drug use (Tanner-Smith et al., 2016b). However, significant variation in the effect sizes was observed (Fig. 1). For example, the three studies at the top of Fig. 1 [i.e., Latessa et al., 2013, (Santa Clara); Sloan III et al., 2004; and Latessa et al., 2013 (Ada)] found that the JDTC did worse than TJC. The 29 studies in the middle [i.e., Latessa et al., 2013, (Clackamas) through Byrnes & Hickert, 2004] found no clear differences (i.e., the 95% confidence intervals (CI) for the effect sizes included the odds ratio value 1.0), and eight of the nine studies at the bottom of the figure [i.e., Mackin et al., 2010 (Anne Arundel), through Supreme Court of Virginia and Virginia Department of Criminal Justice Services, 2003] found that the JDTC did better than TJC (i.e., the 95% CI did not include an odds ratio of 1.0). Some other key findings of the review included: a) the results were similar for recidivism overall and for drug-related crime; b) JDTCs often were not always focused on serving those youth who might benefit the most from them; c) substance use treatment initiation and engagement were often problematic; and d) youth were often referred to psycho-educational substance use education and treatment that were not evidence-based practices. These latter findings suggest a possible reason (i.e., implementation failure) why some JDTCs have better outcomes than others (Sullivan & Latessa, 2011). Perhaps outcomes would have been different had JDTCs been implemented to include evidence-based practices and/or more closely adhere to a set of research-based guidelines.

**Fig. 1 Fig1:**
[figure not shown]
Forest Plot of Effect Sizes from Tanner-Smith et al. (2016a)

Therefore, the Office of Juvenile Justice and Delinquency Prevention developed and published the evidence-based *Juvenile Drug Treatment Court Guidelines* (Office of Juvenile Justice and Delinquency Prevention (OJJDP), 2016) to help JDTCs implement more effective practices reduce the use of ineffective ones, as well as to be consistent with other juvenile justice reform efforts. The JDTC Guidelines (Fig. 2) are organized into 7.

**Fig. 2 Fig2:**
[figure not shown]
OJJDP Evidence-Based Guidelines for Juvenile Drug Treatment Courts (JDTCs). This figure is from the Office of Juvenile Justice and Delinquency Prevention (OJJDP, 2016) *Juvenile Drug Treatment Court Guidelines*. Washington, DC: U.S. Department of Justice, Office of Justice Programs. NCJ 250368. https://ojjdp.ojp.gov/programs/juvenile-drug-treatment-court-guidelines

## Objectives

Focus JDTC philosophy and practice on effectively addressing substance use and criminogenic needs to decrease future offending and substance use and increase positive outcomes;Ensure equitable treatment for all youth by adhering to eligibility criteria and conducting an initial screening;Provide a JDTC process that engages full team and follows procedures fairly;Conduct comprehensive needs assessments that inform individualized case management;Implement contingency management, case management, and community supervision strategies effectively;Refer participants to evidence-based substance use treatment, to other services, and for prosocial connections;Monitor and track program completion and termination.

Within each area, these Objectives were further operationalized into 2 to 6 specific Guidelines (31 total). The current study was developed to test the implementation of these Guidelines and their impact on JDTC outcomes relative to TJC. The following section describes the research design of the study, including its goals, research methodology, and key considerations, particularly implementation fidelity, essential to the interpretability of study findings.

### Evaluation goals and questions

This study is the first cross-site evaluation of the JDTC Guidelines (Office of Juvenile Justice and Delinquency Prevention (OJJDP), 2016). As presented in Table 1, along with specific measurement strategies, this study has 4 major goals, including (1) Determine the extent to which it is feasible to implement the 2016 JDTC Guidelines and the kinds of adaptations courts make to use them; (2) Examine the impact on youth of the JDTC relative to TJC; (3) Identify whether there is evidence for some of the Guidelines being more or less important and/or not important; and (4) Recommend changes to the Guidelines. The specific research questions are:
Do youth with substance use disorders (SUD) experience more positive outcomes if assigned to a JDTC vs. TJC?Are different interpretations of the Guidelines by the courts associated with better outcomes?Are there certain guidelines that, if present, are associated with better outcomes?Are there guidelines that, if absent, do not seem to be associated with worse outcomes?Do some of the seven broad Objectives of the guidelines have a stronger association with outcomes than others?Is there evidence that instances of NOT following the guidelines produce worse outcomes?

**Table 1 Tab1:** Evaluation Goals and Questions and Corresponding Measurement Strategy

Goals	Baseline Interview	Follow-Up Interviews	Records Search	Court Self-Assessment	Site Visit Protocol
Determine the extent to which it is feasible to implement the 2016 JDTC Guidelines and the kinds of adaptations courts make to use them				X	X
Examine the impact on youth of the JDTC relative to TJC	X	X	X		
Identify if there is evidence for some components of the Guidelines being more or less important or not important	X	X	X	X	X
Recommend changes to the Guidelines based on above	X	X	X	X	X

## Method

### Research design and court sites

The cross-site evaluation design involves two parallel studies across 10 sites (defined as a county jurisdiction with a participating JDTC and a participating TJC). As shown in Fig. 3, in two sites, youth who are eligible for JDTC ***and*** TJC are randomly assigned to JDTC vs. TJC. This design provides the most rigorous and direct test of JDTC’s impact relative to TJC. This RCT will be reported according to CONSORT guidelines (Grant et al., 2018).

**Fig. 3 Fig3:**
[figure not shown]
Procedure for Recruitment and Random Assignment of Youth to Study Group (JDTC or Traditional Juvenile Court (TJC) for the Multisite Randomized Controlled Trial (RCT)

As shown in Fig. 4, in the remaining eight sites, youth who are eligible for JDTC ***or*** TJC are assigned to the most appropriate court using a regression discontinuity (RD) algorithm. Per the guidelines, this design means that youth who are at moderate to high risk of recidivism ***and*** have a SUD will be assigned to JDTC and the rest to TJC. Here, the impact of JDTC will be estimated relative to the expected outcome (recidivism) using regression and the TJC data. This design will also provide a test of the Guidelines’ recommended eligibility criteria.

**Fig. 4 Fig4:**
[figure not shown]
Procedure for Recruitment and Assignment of Youth to Study Group (JDTC or Traditional Juvenile Court) for the Multisite Regression Discontinuity Design Study

### Research participants

As shown in Figs. 3 & 4, to be eligible for the cross-site evaluation study, youth must be age 14 to 17 and involved in a juvenile court with a judge presiding (i.e., not including diversion or informal supervision without a judge). For RCT, they must also be eligible for JDTC and TJC. For RDD, they must be eligible for JDTC or TJC. For logistical and practical reasons, youth are excluded from the evaluation study: (a) if they have been adjudicated guilty of a violent offense; (b) if they are expected to move out of the jurisdiction within 12 months; (c) based on judicial or prosecutorial discretion prior to assignment (e.g., someone also being charged with sex crimes or violent offense but not yet convicted); and (d) when the JDTC is already at full capacity. Participation is voluntary and requires the informed assent of the youth and the informed consent of the parent/guardian. After the research team assigns the youth to a condition, the courts can override the assignment and place the youth elsewhere and consent can be withdrawn. Target recruitment numbers were 150 for each of the 10 study sites, yielding a total of 1500 youth with a minimum of 500 in JDTC and a minimum of 500 in TJC. The numbers are expected to vary somewhat as the RD design is based on presenting need/risk (not a fixed ratio).

### JDTC standard training and technical assistance

Two training and technical assistance (TTA) providers were funded by OJJDP to develop training materials and help courts implement the JDTC Guidelines. American University (AU) and the National Association of Drug Court Professionals (NADCP) work with three JDTC grantees who received independent grants for 5 years, and the National Council of Juvenile and Family Court Judges (NCJFCJ) work with seven learning collaborative courts that received training and support for over 3 years. These courts have been approved by NCJFCJ to serve as model JDTCs that are interested in changing practices to improve operations and outcomes. Monthly calls between the research team and the TTA providers and sites are used to monitor training, and monthly calls with research sites help the research team stay abreast of site-level data collection activities and answer questions about the research design.

### Data collection procedures

As show in Table 1, data collection is guided by the goals of the study. It involves measures at both the study participant level (i.e., baseline and follow-up interviews, administrative court records) and the site level (i.e., Court Self-Assessment and research site visits). The former measures are specifically focused on comparison of JDTC and TJC interactions with youth (supervision, drug testing, service provision, etc.), which are hypothesized to determine efficacy of JTDC, and the latter measures are focused on understanding the feasibility and degree of implementation of the guidelines and determining whether some have a greater impact than others. Data collection is facilitated by site-based research liaisons (a person local to the research site who is trained on the study procedures and who serves as the first-tier responder to questions from program and evaluation staff), by facilitating communication between the site and evaluation teams to obtain the youth survey data, as well as the abstraction of administrative data from the youths’ juvenile justice records including local and statewide jurisdictions. The data on the implementation of the courts are collected via semi-structured multiple-day site visits by researchers at Carnevale Associates, LLC, and the collection of the Court Self-Assessment data is coordinated by researchers at NPC Research.

#### Youth survey

As show in Table 2, a baseline survey is collected from youth prior to their assignment to study condition, and again at 6 and 12 months following (i.e., follow-up) their assignment. Youth receive an incentive of $5 for baseline, $15 for 6-month follow-up, and $20 for 12-month follow-up (for a maximum total of $40) disbursed on McDonald’s gift cards. The baseline and follow-up surveys are designed to take 25 to 30 min to complete, and include numerous empirically validated assessments, including the Global Assessment of Individual Need Q3 (GAIN Q3; Titus et al., 2013), Mental Health Continuum Short Form measure of mental well-being (MHC-SF; Keyes & Simoes, 2012; McGaffin et al., 2015), the Family Effectiveness Measure (FAM; McCreary et al., 2013), the National Mentor Resource Center’s (NMRC) “Very Important non-parent Adult” (VIA; Herrera et al., 2007), Social Environment Scale (SES; Godley et al., 2005), the structured activity scale from the National Mentoring Resource Center Out of School Time (OST; Scales et al., 2006), and the Global Assessment of Individual Need Short Screener (GAIN-SS; Dennis et al., 2006). An evaluation liaison and up to two additional staff in some sites have been trained and certified in administering the study survey by the cross-site evaluation team led by Chestnut Health Systems. These staff administer the interview on the project’s web-based software, GAIN ABS, in person or by phone/Zoom® video conferencing to youth after obtaining informed assent/consent from the youth and their parent/guardian (baseline), as well as at 6 and 12 months later. In response to a drop off in follow-up surveys after COVID emerged, the study also introduced the option for youth to self-administer the follow-up via the web service. Youth survey data are downloaded quarterly and reviewed for inconsistencies and/or missing data; data from these instruments will also be compared to the published psychometrics from their original sources.

**Table 2 Tab2:** Summary of Data Collected for the JDTC Guidelines Cross-Site Evaluation Project

Data Collection Instrument	Source of Instrument	Data Collection Interval	Party Coordinating Data Collection
Youth Surveys Sections		Baseline, 6 & 12 Month Follow-up	Local Liaison, Chestnut Health Systems
A. Exclusion and Consent Checklist, start time, time anchoring	GAIN Q3 (Titus et al., 2013)	”	”
B. Background Information	GAIN Q3 (Titus et al., 2013)	”	”
WB. Wellbeing	Mental Health Continuum Short Form (Keyes & Simoes, 2012; McGaffin et al., 2015)	”	”
FE. Family Environment	Family Effectiveness Measure (FEM; McCreary et al., 2013) and Very Important Adult (VIA; Herrera et al., 2007) questions from National Mentoring Resource Center (NMRC)	”	”
SP. School and Peers	GAIN Q3 (Titus et al., 2013), Social Environment Scale (SES; Godley et al., 2005) and Out-of-School Time (OST) structured activity scale from National Mentoring Resource Center (Scales et al., 2006)	”	”
RB. Risk Behavior	GAIN Q3 (Titus et al., 2013)	”	”
MH. Mental Health	GAIN Q3 (Conrad et al., 2010; Conrad et al., 2012; Titus et al., 2013)	”	”
SU. Substance Use	GAIN SS (Dennis et al., 2006; Garner et al., 2013; Riley et al., 2007)	”	”
CV. Crime and Violence	GAIN SS (Conrad et al., 2010; Dennis et al., 2006; Garner et al., 2013)	”	”
Z. End	GAIN Q3 (Titus et al., 2013)	”	”
XADM Administration	GAIN Q3 (Titus et al., 2013)	”	”
Youth Record Abstraction	JJTRIALS youth records data funded by NIDA (Belenko et al., 2017) and JDTC Guidelines funded by OJJDP (2016)	Continuously throughout project	Local Liaison, Chestnut Health Systems
JDTC Court Self-Assessment	JDTC cooperative tool funded by OJJDP to measure implementation of the 2016 JDTC Guidelines	Spring 2018, Spring 2020	NPC Research
TJC Self-Assessment	Abbreviated version (omits specific JDTC-focused) questions of JDTC Court Self-Assessment	Spring 2018, Spring 2020	NPC Research
Site Visit Protocol	RWJ RF JDTC Evaluation (Greene et al., 2014) and JDTC Guidelines funded by OJJDP	Fall 2018 to Winter 2020	Carnevale Associates, LLC

Notes: *GAIN Q3* Global Assessment of Individual Need Q3, *GAIN SS* Global Assessment of Individual Need Short Screener, *JJTRIALS* Juvenile Justice Translational Research on Interventions in Adolescents in Legal Settings, *NIDA* National Institute on Drug Abuse, *OJJDP* Office of Juvenile Justice and Delinquency Prevention, *RWJ* Robert Wood Johnson, *RF* Reclaiming Futures

#### Youth juvenile justice records

Based on a procedure used in a prior multisite study of a process improvement intervention designed to reduce unmet substance use service needs among juveniles on probation (Dennis et al., 2019, b), juvenile justice records are abstracted by JDTC staff at each local research site to record each study participant’s history of prior arrests, current charges, changes in courts, dispositions, and rearrests during the 12 months following assignment to study condition. In addition, the sites extract data on assessment and treatment using the Behavioral Health Services Cascade framework (Belenko et al., 2017; Dennis et al., 2019, b). Abstracted data are uploaded monthly and the site evaluation liaison is given feedback on the quality of site records data submissions each quarter.

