### Primary outcomes

#### Recidivism

For this study, recidivism is measured both by self-report on the follow-up surveys, as well as through juvenile justice records abstraction which includes information retrieved from local and statewide databases on new arrests. Consistent with the OJJDP’s recidivism workgroup (Harris et al., 2011), operational definitions for recidivism will be derived separately for self-report and official records, as well as a combination of these information sources, and will focus on new arrests following assignment to study condition, with measures reflecting whether any new arrest occurred (0 = No, 1 = Yes), the number of new arrests, as well as subsets of these arrests based on major offense types including property, violent, public disorder, and substance possession (including alcohol). Specific arrest dates will be collected for each, enabling analyses to consider the latency (i.e., length of time) between study assignment and date of arrest.

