Youth-level data collection procedures also evidence significant strengths. For example, self-reported data, much of which is typically not the part of official administrative records, will be used to collect both the primary (i.e., recidivism and drug use) and secondary outcomes (e.g., mental health and wellness), enabling direct comparisons between JDTC and TJC youth on each of these outcomes. Importantly, these self-reported data are collected using an interview that incorporates numerous instruments with known measurement properties for the same populations being studied. This approach significantly enhances confidence regarding data validity and reliability. Moreover, the interview data are collected three times during the course of the study; baseline, 6 months, and 12 months post-program entry. The use of multiple comparable time frames for these data enables comparison between JDTC and TJC youth on both primary and secondary outcomes at each time point, as well as change over time. When combined with the data on guideline implementation and the degree to which services overlap between JDTC and TJC conditions, analyses will be able to provide a clearer picture regarding the degree to which youth in each condition change (for better or for worse) while controlling for other potentially confounding variables.

Outcome data also are being abstracted from the administrative records, which include local and state-wide information for both JDTC and TJC youth. These data are valuable for comparison to the self-report data for establishing its concurrent validity. In addition, the degree to which findings observed in the self-reported data (i.e., between-group differences in recidivism and drug use) also are found in the administrative data will enhance the construct validity of research findings regarding the effectiveness of the JDTC programs. An added benefit of the administrative data is that specific event dates (e.g., date of a new arrest, date of a positive drug assay) will be recorded. This detail enables event history analysis of the relative risk ratios over time between groups and considers the unique aspects of data (e.g., censoring), as well as differences in risk ratios to specific time points (operationalizable in both days, weeks, and months) tested, such as time to first arrest, or number of days of negative drug tests.

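### Rearrest records for both arms are abstracted by staff of the court under test, with no masked or uniform search described, so capture could differ by arm

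*Protocol article*

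**What the plan says.** In its section on youth juvenile justice records, the protocol article states that "juvenile justice records are abstracted by JDTC staff at each local research site". The task covers each study participant and includes "dispositions, and rearrests during the 12 months following assignment to study condition". The same abstraction covers "history of prior arrests, current charges, changes in courts, dispositions".

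Under Primary outcomes, the Recidivism subsection says that "recidivism is measured both by self-report on the follow-up surveys, as well as through juvenile justice records abstraction". The records component rests on "information retrieved from local and statewide databases on new arrests". Definitions are to be built from self-report, from official records, and from the two combined. The Discussion describes the administrative data as records "which include local and state-wide information for both JDTC and TJC youth".

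The only check described on the abstraction is quarterly feedback to the site liaison on the quality of the monthly uploads. The limitations in the Discussion cover the truthfulness of youth reports, the non-random choice of courts, and cross-over between conditions. They do not mention who abstracts the records.

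**The concern.** Staff of one of the two courts being compared ascertain a primary outcome in both. They can be expected to know which youth are on their own docket, and the changes of court and dispositions that they record show the court in any case. They also belong to the programme whose effect is being judged.

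The event is objective, but finding it takes work: someone must search local and statewide sources, match the youth and enter the arrest. If that search is fuller for one arm, the recorded rates differ without any true difference. Greater familiarity with JDTC youth could raise capture in that arm and count against JDTC. A stake in the result could lower it and favour JDTC.

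Neither design removes this. Randomisation balances the youth at baseline, not the later search for their arrests. In the eight regression-discontinuity sites the assigned court changes at the cut-score, so a difference in capture by court would change there too and could pass for an effect.

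**Working it through.** **1. What the text establishes.**

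- Abstractor: JDTC staff (section on youth juvenile justice records).
- Coverage: every participant, in both conditions (same section; Discussion).
- Outcome: rearrest over 12 months, a source for a primary outcome (Recidivism subsection).
- Knowledge of the arm: an inference. The article does not use the word unblinded, but it follows from the abstractors' employer and from the court-process items they record.
- Masked, duplicate or standardised search: none described.

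**2. Illustration of size.** The article gives no rearrest rate, capture rate, significance level or allocation ratio, so there is no planned figure to reproduce. The assumptions are:

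- no true difference between arms;
- two-sided 5% test;
- 150 per arm, from two randomised sites × 150 youth = 300, split equally;
- true rearrest p of 30% to 50%;
- capture of 95% in one arm and 90% or 85% in the other.

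Recorded rate = p × capture. For p = 0.40:

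- 0.40 × 0.95 = 0.380
- 0.40 × 0.85 = 0.340
- spurious gap = 0.040

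Standard error = √[(0.38 × 0.62 + 0.34 × 0.66)/150] = 0.0554, so z = 0.040/0.0554 = 0.722.

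False-positive chance = Φ(0.722 − 1.96) + Φ(−0.722 − 1.96) = 0.108 + 0.004 = 0.112, about 11%.

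The same formula over the assumed range, at 150 per arm:

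| True rearrest | Capture | Recorded rates | Gap (points) | False-positive chance |
|---|---|---|---|---|
| 30% | 95% vs 90% | 28.5% vs 27.0% | 1.5 | 6.0% |
| 40% | 95% vs 90% | 38.0% vs 36.0% | 2.0 | 6.5% |
| 50% | 95% vs 90% | 47.5% vs 45.0% | 2.5 | 7.2% |
| 30% | 95% vs 85% | 28.5% vs 25.5% | 3.0 | 9.0% |
| 40% | 95% vs 85% | 38.0% vs 34.0% | 4.0 | 11.2% |
| 50% | 95% vs 85% | 47.5% vs 42.5% | 5.0 | 14.0% |

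With equal capture the formula returns 5%. Swapping the arms reverses the sign of the gap and leaves the probabilities unchanged.

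**3. Why the illustration stops at 150 per arm.** The article's minimum of 500 per condition pools the randomised and regression-discontinuity sites. In the latter, youth are assigned by recidivism risk and substance use disorder, so equal true rates and a simple two-proportion test do not describe the comparison.

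**The case against.** The strongest reply is that little judgement is involved. An arrest is a dated event in a database, not a rating, and the sources include statewide systems. Self-report supplies a separate measure, and the Discussion plans to compare it with the records. Uploads are monthly, with quarterly feedback on quality. Some JDTC and TJC staff are shared, so any gap in familiarity may be small at some sites. All of this stands, and it is why the point is a risk to reduce and not a fatal flaw. It does not remove the risk. No identical search for both arms is described, the quality feedback is not said to compare capture by arm, and the article reports that follow-up surveys dropped off after COVID, which weakens self-report as a check.

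A reader might infer several stronger things that the article does not support:

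- *That it contradicts itself on who abstracts.* Table 2 lists "Local Liaison, Chestnut Health Systems" for record abstraction, but that column names the party coordinating collection. The liaison, described as "a person local to the research site who is trained on the study procedures", is said to facilitate the work. Both roles fit with JDTC staff doing the abstraction.
- *That JDTC staff hold fuller files on their own youth or supervise them daily.* Neither is stated, so no direction of bias can be claimed.
- *That nothing could be done at analysis.* Agreement between self-report and records, compared by arm, could at least reveal differential capture.

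**Conclusion.** The point holds as a risk of bias that a change of procedure can reduce. The article states outright that staff of the evaluated court abstract rearrests for both arms. It describes no masked or uniform search and does not list this among its limitations. That bias occurred, or in which direction, is not shown.

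On assumed rates and 150 per arm, a capture gap of 10 percentage points gives a spurious difference of 3 to 5 points and a false-positive chance of about 9% to 14%. A gap of 5 percentage points gives 1.5 to 2.5 points and about 6% to 7%. These figures show sensitivity to differential capture; they are not estimates of this study's error rate. The change should be made, but the point does not invalidate the recidivism outcome.

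**What to change.** Amend the section on youth juvenile justice records as follows.

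1. Obtain 12-month rearrests by one fixed query of local and statewide sources, identical for every youth, run after that youth's month 12 from an identifier list without court assignment.
2. Have the existing research liaison run it where that person has access to the records and is not JDTC staff. The article establishes neither for every site, so each site should confirm both.
3. Limit JDTC staff to service, treatment and court-process data.
4. Keep both local and statewide arrests in the primary definition. Nothing in the article shows that statewide data alone are complete.
5. Report agreement between records and self-report by arm, using data already collected.
6. Add the abstractor's role to the limitations, including for any records already abstracted by JDTC staff.

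The cost is small: a task is reassigned, a query is written down, and access to records may need arranging at some sites. A masked duplicate abstraction of a sample would be a further check, but it would need extra staff.
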